## Methods

### Study Design Overview

The study consists of 3 phases, with Phase I and II addressing Aim 1 and Phase III addressing Aim 2 (Figure 1). During Phase I, the previously developed content will be refined and modernized. Both digital health apps will also be developed. In Phase II, the usability and acceptability testing will be completed for patients and pharmacists. During Phase III, Aim 2 will be assessed by pilot testing the digital health app to assess medication adherence and health outcomes.

**Figure 1. F1:**

Development of patient and provider diabetes digital health apps.

### Phase I

During this phase, we want to inform the design of the digital health app with evidence-based instructional principles. Therefore, to maximize the effectiveness of the digital health app, the content should promote and embrace effective learning. As a result, content will be refined to ensure the educational component is bidirectional, educational principles are used to maximize multimedia learning, general medication information is included, and cost and security concerns are addressed. Overall, the content will be improved for digital learning. The content will then be transferred into the Patient digital health app, containing 3 modules. While developing the content, we will adapt Gagne’s Nine Events of Instruction (GNEOI) as an overarching evidence-based strategy to support the effectiveness of the new app [32]. GNEOI is aligned with best practices derived from cognitive psychology and information processing theory. It includes the following sequence of events for organizing learning: (1) gain learners’ attention, (2) inform learners of objectives, (3) stimulate recall of previous knowledge, (4) present the content, (5) provide learning guidance, (6) elicit performance, (7) provide feedback, (8) assess performance, and (9) enhance retention and transfer. Within the overarching GNEOI strategy, our team will modernize and improve the multimedia learning of the app by tailoring the content following Mayer’s 12 principles of cognitive theory of multimedia learning [33]. These principles, also firmly grounded in information processing theory, include providing text, graphics, and narration that support learning goals, keeping visuals simple, avoiding distractions (eg, unnecessary background music), using human voiceover, and adhering to the redundancy principle (eg, allowing the patient to select graphics and narration vs graphics and text). We will use whiteboard animation software to convert written content into approximately 30‐60–second videos. Whiteboard animation consists of using simple animation to teach concepts that follow many of Mayer’s 12 principles. Data suggest whiteboard animation can assist with increasing patient and caregiver information retention [34]. These animations can be tailored to different populations (eg, by changing skin tones or language and adding closed captioning). By following Mayer’s 12 principles, the content will support knowledge construction in which the patient is building a coherent mental representation from the information presented. Please note that for Phase I, no participant recruitment will be needed.

#### Module Content

There are 3 modules guided by the enhanced information-motivation-behavioral (IMB) model for diabetes, which allows for bidirectional learning and fits squarely within the overarching GNEOI strategy. The IMB skills model provides an actionable plan to design and implement digital health interventions [35,36]. For example, the patient is asked a question about information they just saw or read. If they answer correctly, the module congratulates them and moves on to another topic; if they do not, the module summarizes the content in a follow-up slide or video and asks the question again. (Figure 2). Overall, the IMB model proposes that if individuals receive the information they need, feel motivated to modify their actions, and apply the necessary skills, it may provide sustained behavior change that promotes adherence and health outcomes [35,36].

**Figure 2. F2:**
[figure not shown]
Bidirectional learning model.

The first module provides general information on T2D (eg, the role of insulin) and asks questions about mental health and family support. The second module provides information on diet, exercise, the benefits of medication adherence, and methods of monitoring T2D. The module also asks the patient if there are specific areas they would like to explore further (eg, diet, exercise, vaccinations, and glucometer use). For example, the module will not only discuss the benefits of using a glucometer but will also ask if they use or need one, thereby alerting the pharmacist of the need to secure one for the patient before the next counseling session. The third module allows patients to select their prescribed medications, provides information about those medications, and asks about their ability to administer them. For example, if a patient states they take insulin, the module will provide information about insulin and then ask if they have fears about injecting it and if they would like additional instructions on proper administration. This information will allow the pharmacist to develop an individualized CMM plan focused on specific needs for each patient.

After the content is refined and modernized, 2 diabetes experts and an instructional design expert will review it and provide feedback. The content will then be updated based on their input, and the app developer will create 2 digital apps: the Patient and Provider apps. The Patient app will house the 3 modules. Patients will be able to easily download it to a mobile device using the app stores on iOS (eg, Apple iPhone) or Android (eg, Google phone). Based on preliminary discussions with the app developer, the app will fit into a 16×9 (1920×1080 pixels) aspect ratio and can be adapted to various formats (eg, smartphone and tablet). A narrated voiceover option will also be included. Therefore, the app will be accessible to patients who may be illiterate or have some visual problems (eg, mild-moderate diabetic retinopathy).

After the patient downloads the digital app and completes the 3 modules, the app will encrypt the patient’s responses and generate a QR code. QR codes are used to package and transmit information securely, and their use has become more widespread, even becoming a recent function on Windows, allowing a user to convert a webpage into a QR code. QR codes provide an effective and secure method of transmitting patient responses directly to a provider who uses the Provider app. The QR code will contain all the encrypted information captured from the patient’s responses and does not have to be uploaded to the cloud, where the information could be compromised. More importantly, the patient’s responses contained within the QR code cannot be decrypted without the Provider app. The patient will have the option to send their QR code via email ahead of time or provide it at their follow-up appointment. The Provider app will be used by the clinic to decrypt the data stored in the QR code using a concept in computer science known as asymmetric cryptography, which is the industry standard. This technology allows for the creation of a lock made of an unpredictable, large, and randomized series of numbers embedded in the QR Code, which can only be decrypted using a private key (eg, the Provider app). Once the QR code is scanned by the clinic pharmacist using the Provider app, the pharmacist will be able to access the patient’s responses, presented in a user-friendly format. Although the modules and patient responses in the Patient app will be in Spanish, the information will be available in the Provider app in either English or Spanish according to the pharmacist’s preference.

### Phase II

During this phase, usability and acceptability testing by patients and pharmacists will be completed. To screen the patients, we will assess their language dominance using the Language Experience and Proficiency Questionnaire [37]. We will assess the patients’ acculturation level using the scale developed by Marin et al [38]. This 12-item acculturation scale has been widely used in research on Hispanic individuals. Acculturation, as measured by this scale, correlates highly with respondents’ generation, length of residence in the United States, age at arrival, and ethnic self-identification. We will use criterion sampling to recruit up to 20 older Hispanic patients with T2D and low acculturation.

#### Patient Usability and Acceptability Testing

A recent systematic review of usability research in educational technology found that many studies are narrowly focused and insufficiently iterative, leading to results that fail to support the user experience as comprehensively as possible [39]. A frequent problem is the application of unimodal approaches that apply a single questionnaire to obtain a summative measure of overall quality. In contrast, our patient usability and acceptability testing will apply a robust set of methods intended to iteratively improve the quality of the design, promoting a highly usable and acceptable experience. This will include repeatedly triangulating results from cognitive “think-aloud” interviews, screen recordings, and the previously validated SUS and AEOUS [40,41]. A previously used questionnaire based on Davis’ TAM will also be used to evaluate system acceptability [22,42]. In summary, a set of 5 patients (seen separately) will be observed interacting with the Patient app and will be asked to “think out loud” so that their cognitive processes can be tracked and areas of difficulty can be identified as they review the modules [43,44]. Simultaneously, their screens will be recorded, and transcripts will be produced and timestamped for analysis. After each session, the SUS, AEOUS, and TAM will be administered to provide a snapshot of system quality. The app and content will be revised based on these results, tested with a new group of 5 participants (seen separately), and revised further [45]. This process may be repeated until no further difficulties are identified and benchmark SUS, AEOUS, and TAM scores are obtained, potentially eliciting responses from 15 to 20 participants [46,47]. Previous literature has indicated that small convenience samples are highly effective in software studies [48]. A sample size of 10 should be sufficient based on previous experience [22]; however, since we will also be evaluating the app and content on different devices, we will target up to 20 participants.

#### Pharmacist Usability and Acceptability Testing

We will test the usability and acceptability of the intervention for incorporation into CMMs with up to 10 pharmacists. Pharmacists will be recruited from our collaborative clinic (Athens Neighborhood Health Center) and other federally qualified health centers that work with Hispanic patients and the CMM process. We will conduct individual interviews with the pharmacists to test the intervention and obtain feedback (eg, SUS, AEOUS, and TAM scores) to improve the ease and practicality of use when conducting CMM. They will also test and evaluate the Provider digital app to identify the optimal method of displaying patient responses. Our previous study tested much of the content with pharmacists and required 1 round (5 individual interviews) [22]. However, since we are also focused on developing the digital app for pharmacists, we budgeted for 10 pharmacists in case 2 rounds of testing are needed to make sure the Provider app is user-friendly.

### Phase III

The third phase will test health outcomes: medication adherence, HbA_1c_, and fasting blood glucose. During this phase, the pharmacist will use the digital health app with 40 adult Hispanic patients with T2D who meet the inclusion requirements (stated under the ”Recruitment” section). The study will take place at the Athens Neighborhood Health Center. If by 6 months, we have not recruited at least 25 patients, we will pursue another local federally qualified health center. After consent, patients will be instructed on downloading the digital health app, completing the modules within the first 2 weeks, and generating the QR code. Their preference for either submitting the QR code via email or bringing it to their next appointment will be confirmed. Medication adherence will be measured using scales previously used by the investigators (the Gonzalez-Lu questionnaire and the visual analog scale) [49,50]. The Gonzalez-Lu questionnaire and visual analog scale are being used due to their ease of use and strong reliability and correlation to electronic measurements of medication adherence [51-53]. Baseline HbA_1c_ and blood glucose levels (fasting) will be measured via labs conducted as standard medical practice. A follow-up visit will occur 3‐4 months later. Depending on patients’ responses, an additional visit 3‐4 months later may be needed. The app would immediately assist a patient who is nonadherent due to not knowing how to take a medication (eg, the app would explain that taking metformin with food optimizes effectiveness and lowers side effects). However, a patient may be nonadherent due to the inability to pay for a particular medication; this would be captured by the app but not addressed immediately because they chose to provide their QR code at the follow-up appointment and not when the issue arose. In such a scenario, the patient would have a follow-up visit an additional 3‐4 months after appropriate changes are made (eg, selecting another medication). In summary, Phase III will test our Aim 2 hypothesis that the app will improve medication adherence (>80% average adherence for the individual), HbA_1c_ (≥0.75% reduction), and fasting glucose (≥25% reduction) from baseline. These reductions are reasonable target endpoints based on the literature [54-56].

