### Recruitment

Two types of participants will be recruited for Phase II: patients and pharmacists. Patients (n=20) asked to participate will be Hispanic men and women aged 50 years and older with T2D who have been on diabetes medications for at least 90 days but who are not adherent (ie, <80% adherent) and have increased diabetes markers (ie, HbA_1c_ >7% and fasting glucose >125 mg/dL). In addition, they should be able to meaningfully participate in the informed consent process, demonstrate poor acculturation based on the Marin Acculturation Scale, be comfortable speaking Spanish (during the preconsent or consent process), have and use a smartphone or tablet, and be willing to participate in a single visit lasting approximately 90 minutes. Exclusion criteria will include cognitive or psychiatric difficulties so severe as to make the person unable to meaningfully participate in the informed consent process, diagnosis of Alzheimer disease or any other dementia, or receiving pharmacotherapy for Alzheimer disease, and severe retinopathy or visual impairment that impacts the ability to see module content on a smartphone or tablet. Pharmacist participants (n=10) asked to participate will be licensed pharmacists providing CMM to Hispanic patients with T2D in an ambulatory care setting. In addition, they should be able to meaningfully participate in the informed consent process and be willing to participate in a single visit lasting approximately 90 minutes.

Only patients will be recruited for Phase III. Patients asked to participate will be Hispanic men and women aged 50 years and older with T2D who have been on diabetes medications for at least 90 days but who are not adherent (ie, <80% adherent) and have increased diabetes markers (ie, HbA_1c_ >7% and fasting glucose >125 mg/dL). Inclusion criteria will be similar to those in Phase II. However, they must be willing to participate in a baseline office visit and 1‐2 subsequent follow-up office visits lasting 60‐90 minutes, with each visit spaced 3‐4 months apart. Exclusion criteria are similar to those described in Phase II.

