### Procedures

Before the recruitment process, University of Georgia Institutional Review Board (IRB) approval for the proposed human participants research protocols will be secured, as well as any review required by the Athens Neighborhood Health Center. The study will also be registered on the United States government clinical trials website.

Overall, potentially eligible patient participants (for Phase II and III) will be recruited from patients at the Athens Neighborhood Health Center during their regular appointments. In addition, bilingual flyers will be posted in the clinic’s waiting room. Patients will be able to contact the investigator or clinician via email or phone call in English or Spanish to obtain more information about the study and/or express their interest in the study. Once patient participants are identified, a telephone screening or face-to-face interview in Spanish will be conducted for each potential participant. During the screening interview, participants will be informed of the nature of the study and may participate if interested and if the eligibility criteria are met. If they choose not to participate, they will be thanked for their interest and reminded that not participating does not impact their standing with the clinic. Potential pharmacist participants for Phase II will be recruited from the clinic site and locally (in the state of Georgia), as well as from other states serving Hispanic populations. As a result, it is important to note that pharmacist participants may be remotely interviewed via a secure server (ie, Zoom Meetings software) during Phase II. While pharmacists will have the option for remote interviews, visits for patient participants will all be conducted in person (face-to-face).

#### Aim 1

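### Phase III lets patients keep the completed QR code until the 3–4 month visit, so a high PHQ-2 or other barrier can go unread for about 77–122 days if there is no earlier clinic contact

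*Protocol article*

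**What the plan says.** The Phase III section asks patients, after consent, to download the app, "completing the modules within the first 2 weeks", and to generate the QR code. On delivery it says: "Their preference for either submitting the QR code via email or bringing it to their next appointment will be confirmed". The description of the QR code under Phase I, Module Content, names the same two routes: "The patient will have the option to send their QR code via email ahead of time or provide it at their follow-up appointment". It adds that the encrypted responses can be opened only with the Provider app.

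The first follow-up is 3–4 months after baseline. Under Recruitment, "they must be willing to participate in a baseline office visit" plus one or two follow-up visits, each 3–4 months after the one before. No study visit lies between baseline and the first follow-up.

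Phase III works through one case: a patient who cannot afford a medicine. The barrier is "captured by the app but not addressed immediately because they chose to provide their QR code at the follow-up appointment". The text continues "In such a scenario, the patient would have a follow-up visit an additional" 3–4 months once changes have been made.

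The modules also ask about mental health, family support and supplies. For a patient who needs a glucometer, Module Content speaks of "alerting the pharmacist of the need to secure one for the patient before the next counseling session". The Discussion (Principal Findings) says the Patient app will carry the PHQ-2, and that the Provider app alerts the pharmacist to a high score after decryption.

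**The concern.** The trial collects a depression screen and practical barriers in weeks 0–2, yet lets the patient decide whether the pharmacist sees them then or months later. A patient who holds the code, and has no other contact with the clinic, gives answers that nobody in the clinic can read until the first follow-up visit.

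Two things are at stake. The first is care: a high PHQ-2, a missing glucometer or an unaffordable medicine can wait for most of the first study interval although an email route already exists. The second is description of the intervention. For a holder, adherence, HbA1c and glucose at the first follow-up reflect the baseline CMM session (Abstract, Methods) and the app's education, but not counselling informed by the patient's own responses, which is what the Provider app is for. The Aim 2 section intends to use the effect size to plan a larger trial, and its readers will want to know how much of the Provider app had been delivered when those outcomes were measured.

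**Working it through.** The plan states no delay in days, so there is no figure to reproduce. The wait follows from its timings.

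**Inputs**
- Module completion: day 0 to day 14 (Phase III).
- First follow-up: 3–4 months after baseline (Phase III, Recruitment).
- Month length: 30.44 days (my assumption).
- Consent and baseline on the same day (my assumption; the article does not say).
- No clinic contact before the first follow-up at which the code is scanned (a condition, not a claim about every patient).

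**Wait from completed modules to first possible reading, for a patient who holds the code**

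Wait = day of first follow-up − day of module completion.
- First follow-up: 3 × 30.44 = 91 days to 4 × 30.44 = 122 days.
- Shortest wait: 91 − 14 = 77 days (11 weeks).
- Longest wait: 122 − 0 = 122 days (about 17 weeks). This end needs completion on day 0 and a visit at 4 months.
- Completion on day 14: 91 − 14 = 77 to 122 − 14 = 108 days.

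**Sensitivity to month length**

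| Days per month | Shortest (3 months − 14 days) | Longest (4 months − 0 days) |
|---|---|---|
| 28 | 70 | 112 |
| 30 | 76 | 120 |
| 31 | 79 | 124 |

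The conclusion does not depend on the convention.

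**What the additional visit changes.** It falls 3–4 months after the first follow-up: 6 × 30.44 = day 183 to 8 × 30.44 = day 244. It gives a holder with an unaddressed barrier a later outcome, taken after changes have been made. The first reading still happens at day 91–122, so the wait above is unchanged.

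**How many patients.** The share who will hold the code is not given. At an assumed 10%, 25% or 50% of 40 it would be 4, 10 or 20 patients.

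**PHQ-2 against cost.** The cost delay is written into Phase III with a response. For a high PHQ-2 the only step described is the Provider app's alert, which comes after decryption.

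**The case against.** The strongest reply is that the delay is disclosed and chosen. Phase III describes it for cost barriers, says such a patient would have a further visit, and the 3–8 month window under Aim 2 accommodates that visit. In-person hand-over also has a reason: Limitations expects some older adults to struggle with technology. This stands as far as it goes. The plan does not contradict itself here, and hand-over should be kept. It does not answer the wait itself, which the extra visit leaves as it is, nor the PHQ-2, which the example does not cover.

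A second reply is that the patient may bring the code to the next appointment, that patients are recruited "during their regular appointments", and that clinic pharmacists already manage their diabetes. An earlier routine visit would shorten the wait. That is right, and it is why the range applies only to holders without such contact.

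A third reply is that an article condenses the full protocol, and that an on-screen message for a high PHQ-2 could be specified there or in the submission for ethical review. That also stands, and the fix is conditional on it. The hold option, the visit spacing and the alert after decryption, however, are positively written.

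A reader might infer that emailing gains a patient 77–122 days of response-informed counselling against none for a holder. The documents do not support that. Phase III implies that earlier sending allows earlier action, but nothing says when an emailed code is read, and CMM is described only at baseline and follow-up visits. The figure is at most an upper bound, and asking for email alone would not secure it.

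**Conclusion.** The point holds, and is worth fixing before Phase III. Under the plan as written, a patient who finishes the modules by week 2 and keeps the code can have a high PHQ-2 or another barrier go unread for about 77–122 days, or 77–108 days if the modules are finished on day 14. This assumes that consent and baseline coincide and that there is no earlier clinic contact. The number of patients affected is unknown.

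Two stronger readings are not supported. One is that the Aim 2 estimate is biased or the study loses power. The pooled change over 3–8 months remains valid for the apps as offered, patient choice included; it simply mixes patients with and without the Provider-app step by the first follow-up. The other is that holders are left without any later outcome. Those with an unaddressed cost barrier are stated to receive the additional visit, and further visits depend on patients' responses, so holders without one may largely be those whose answers called for no change.

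**What to change.** In Phase III:

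1. Ask patients by default to email the code, or have it scanned, when they complete the modules. Keep hand-over at the visit as a fallback.
2. State a short time within which the pharmacist reads a sent code. Without this the new default does not guarantee earlier action.
3. Have the Patient app itself show a patient with a high PHQ-2 a message to send the code or contact the clinic. This needs no cloud upload, so the privacy rationale is kept. If the full protocol already does this, say so in the article.
4. Record decryption dates, report how many first follow-up outcomes preceded decryption, and describe the effect size as that of the apps as offered.

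The cost is a changed instruction, a reading-time rule, one in-app message, a date field and one reported count. Patients lose a little choice, and pharmacists spend some reading time earlier. The Results section reports that only the Phase II portion has gone to ethical review, so Phase III can still be changed.
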